### Final prognostic model

The optimised adjusted calibration slope will then be used as a uniform shrinkage factor. Each of the coefficients from the original model will be adjusted for by multiplying by the shrinkage factor. The intercept will also be adjusted to ensure calibration-in-the-large, the average predicted probability, is the same as the average observed probability.

### Secondary analysis

Using the secondary outcomes, we will repeat the steps above to create a supplemental final prognostic model, for survival to PICU and survival to 3 months. In addition, we will create a prognostic model for good neurodevelopmental outcome using POPC and PCPC outcome scores.

There is a potential for survivors to decline consent, be lost to follow-up, or fulfil the exclusion criteria into the NEUROPACK study, and therefore, there is a risk that the survival subgroup may be biased. We plan to undertake sensitivity analyses by (1) imputing missing VABS II score for survivors using their known PICANet and NETPACK 3 data, (2) assume all survivors without a neurodevelopmental score had a VABS II score ≥70 and (3) assume all survivors without a neurodevelopmental score had a VABS II score <70, to ascertain impact of this group on the final prognostic model.

In addition, due to the limitations of not having a baseline VABS II score, we will also perform a secondary analysis using VABS II score ≥70 as the good neurodevelopmental outcome for a subgroup of patients with a known baseline PCPC score 1–3. This will allow comparison of the final prognostic model for all patients and the subgroup with known good neurodevelopment outcome at baseline.

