**Trial registration number:**

NCT03574025.

Strengths and limitations of this studyThis protocol has followed the international recommended Transparent Reporting of a multivariable prediction model for Individual Prognosis or Diagnosis guidelines for the derivation and validation of a clinical prediction model of neurodevelopmental outcome after paediatric cardiac arrest.A nationwide study which will efficiently combine routinely collected data through the existing, high-quality, Paediatric Intensive Care Audit Network database and a bespoke research database.Personalised recruitment and local follow-up will aim to maximise participant retention.The low incidence and wide variety of causes of paediatric cardiac arrest may restrict number of available patients and are potential limitations in prospective prognostic research in this population.Baseline neurodevelopmental status of patients will only be allocated retrospectively using the Paediatric Cerebral Performance Category tool.

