### Recruitment for neurodevelopmental outcome assessment

Parent/guardians of CA patients who are expected to survive to 3 months following CA will be approached by local research staff, trained in Good Clinical Practice, to consent for telephone questionnaire at 3 months post-CA.

This is a very sensitive and difficult time for parents and guardians. The approach to parents or guardians of critical ill children for recruitment to the NEUROPACK study will, therefore, be handled sensitively. Local researchers will be trained to identify the appropriate time to consent, use passive information giving to reduce burden of information (eg, Ethics committee-approved posters displayed in family rooms) and liaise with the medical team managing the patient to acknowledge ongoing clinical management issues. Local site investigator (or delegate) will recontact parents or guardians at 2 months following CA to ascertain continued involvement in the study and to confirm ongoing contact details.

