### Data collections

The ongoing NET-PACK 3 customised data collection and PICANet data collection for the PIM3 risk of mortality will be the data source for all the candidate variables in the NEUROPACK study. Linkage of individual patient NET-PACK 3 data with the collected neurodevelopmental outcome will be carried out for consented patients only. Pseudonymised data from NET-PACK 3 customised data collection and PICANET will be used for patients who die or for patients who survive and consent for follow-up assessment is not available.

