### Secondary outcome assessment

PCPC and POPC scale can be calculated by a short questionnaire conducted at the 3-month follow-up interview for consented patients. A baseline (pre-CA) PCPC and POPC will also retrospectively ascertained at the 3-month follow-up. PCPC and POPC have been recommended for reporting in all paediatric CA studies. They score 1–6 (1: normal, 2: mild disability, 3: moderate disability, 4: severe disability, 5: vegetative state or coma and 6: death). They provide less detail but correlate reasonably well with VABS II.^20^ This will allow comparison with other CA studies. Good neurodevelopmental outcome will be defined as PCPC score of 1–3 or no change from baseline. Poor outcome will be defined as a score of 4 or more, including death. Three months follow-up time point is chosen following the ILCOR, core outcome set for adults after CA recommendation^21^ and demonstration of minimal change between three and 12-month following CA.^22^

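### The secondary analysis in children with known baseline PCPC 1–3 can include only interviewed survivors, so a difference from the all-patient model cannot be attributed to baseline impairment

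*Protocol article*

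**What the plan says.** The Secondary analysis section gives the missing baseline VABS-II as its reason for repeating the VABS-II ≥70 analysis in "a subgroup of patients with a known baseline PCPC score 1–3". It then states the purpose: "This will allow comparison of the final prognostic model for all patients and the subgroup with known good neurodevelopment outcome at baseline".

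Four other places determine who can have a known baseline PCPC:

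- **Secondary outcome assessment**, on the scale itself: "PCPC and POPC scale can be calculated by a short questionnaire conducted at the 3-month follow-up interview for consented patients". On the pre-arrest value: "A baseline (pre-CA) PCPC and POPC will also retrospectively ascertained at the 3-month follow-up".
- **Strengths and limitations list**, after the abstract: "Baseline neurodevelopmental status of patients will only be allocated retrospectively using the Paediatric Cerebral Performance Category tool". No other source of baseline status is named.
- **Recruitment for neurodevelopmental outcome assessment**, on which families are asked: "Parent/guardians of CA patients who are expected to survive to 3 months following CA will be approached by local research staff", to seek consent for the telephone questionnaire.
- **Data collections**: "Pseudonymised data from NET-PACK 3 customised data collection and PICANET will be used for patients who die", and likewise for survivors without consent. Neither the NET-PACK 3 variables listed under Setting nor Box 1 includes a baseline PCPC.

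For the main model, Primary outcome assessment classes death with VABS-II <70 as poor outcome, and Sample size says that all non-survivors enter.

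**The concern.** The subgroup is meant to show what happens to the model when children who were already impaired before the arrest are set aside. That requires the restriction to act on baseline status alone. Here it also acts on survival, because the baseline score is collected three months after the arrest, from families who are interviewed about a living child. Survival is one component of the primary outcome, so the restriction selects on part of what the model predicts.

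The two models then answer different questions. If coefficients, C-statistic or calibration differ, the reader cannot tell whether baseline impairment or the removal of all deaths is responsible. A report that follows the protocol's sentence could present the effect of dropping deaths as an effect of prior disability. It could equally report reassuring agreement that says nothing about baseline status.

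**Working it through.** **Step 1. Who can be in each analysis**

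| Group | Main model | Baseline-PCPC subgroup |
|---|---|---|
| Died | Included, poor outcome | Excluded: registry data only, no baseline PCPC |
| Survived, no interview | No VABS-II; enters only the sensitivity analyses | Excluded: no baseline PCPC |
| Survived, interviewed, baseline PCPC 1–3 | Included | Included |
| Survived, interviewed, baseline PCPC above 3 | Included | Excluded, as intended |

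Only the last row is the exclusion the analysis is meant to make. A consented child who dies before three months falls in the first row, because the baseline score is taken at the 3-month contact.

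**Step 2. Reproduce the planning figures (Sample size section)**

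- Children in 18 months: 250 × 1.5 = 375; the plan states 370.
- Survivors followed up: 370 × 0.50 × 0.80 = 148; the plan states 150.
- Good outcomes: 148 × 0.50 = 74; the plan states 75.
- Events required: 7 × 10 = 70; the plan states 70.

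The chain reproduces to within rounding. I use 370, 148 and 74 below.

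**Step 3. Composition of the main model**

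- Deaths: 370 × 0.50 = 185.
- Analysed: 185 + 148 = 333.
- Good outcome: 74 / 333 = 22.2%.
- Poor outcomes: 185 + (148 − 74) = 259, of which deaths are 185 / 259 = 71.4%.

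**Step 4. What is lost before PCPC is considered**

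- Children removed because they died: 185 / 333 = 55.6%.
- Poor outcomes removed with them: 71.4%.
- Good outcome among those left: 74 / 148 = 50%.

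**Step 5. Sensitivity to the inputs**

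- The Introduction gives survival to PICU discharge of 35%–45% after out-of-hospital and 45%–55% after in-hospital arrest. With 370 children, 80% consent and half of survivors good:
  - at 35% survival: deaths 240.5, followed up 103.6, good 51.8; deaths are 240.5 / 292.3 = 82% of poor outcomes;
  - at 55% survival: deaths 166.5, followed up 162.8, good 81.4; deaths are 166.5 / 247.9 = 67% of poor outcomes.
- The annual figures in Sample size imply 70 / 125 = 56% good among survivors, not 50%. Then good = 148 × 0.56 = 82.9. The good-outcome proportion goes from 82.9 / 333 = 25% to 56%, and deaths are 185 / 250.1 = 74% of poor outcomes.

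**Step 6. After the PCPC restriction**

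The documents give no baseline PCPC distribution. Assume that 70% to 100% of interviewed survivors score 1–3, so n runs from 148 × 0.7 = 103.6 to 148.

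- If all 74 good outcomes are in the subgroup, the proportion good is 50% (74 / 148) to 71% (74 / 103.6).
- If good outcomes are spread in proportion, it stays at 50%.
- If good outcomes were more common among the excluded children, it would fall below 50%.

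**The case against.** The strongest reply has four parts.

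- **The exclusion of deaths is inferred.** The Secondary analysis section never says that deaths are dropped, the words limiting the questionnaire to consented families stand in the sentence on the 3-month score, and the NET-PACK 3 form is a supplement that is not shown. It is true that the form might hold something relevant. But the visible text places baseline PCPC at the 3-month follow-up, names no other source of baseline status, and gives deaths registry data only. A later analysis plan cannot supply a score that was not collected.
- **There is another baseline-aware analysis.** A reader might infer that this subgroup is the plan's only check on the missing baseline. The documents do not support that. The PCPC definition counts no change from baseline as good and death as poor, and the protocol commits to a prognostic model on PCPC and POPC outcomes. Deaths stay in that model without needing a baseline score. Box 1 also has high-risk comorbidity as a candidate predictor. This objection stands and lowers the weight of the point.
- **It is a secondary analysis.** The primary outcome, main model, bootstrap validation, shrinkage and external validation do not depend on it. This also stands.
- **The size is partly assumed.** A reader might infer that the subgroup's good-outcome rate must be at least 50%. It need not be: 50% is the planned rate among followed-up survivors, and the rate after restriction depends on an unstated PCPC distribution. The 185 deaths are deaths before PICU discharge, used here for deaths by three months.

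It would also be too strong to say that no comparison can be made. One can be computed; it does not compare like with like.

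**Conclusion.** The point holds in a limited form. As written, the subgroup consists of interviewed survivors, its model is conditional on survival, consent and interview, and the sentence claiming comparison with the all-patient model does not hold. The distortion is large: deaths are over half of the analysed children and roughly 67% to 82% of poor outcomes across the protocol's own survival range.

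This rests on two assumptions: that the protocol's text is complete about where baseline PCPC comes from, and that the planning rates are roughly right. It does not mean that the main prognostic model is biased, or that baseline function is otherwise ignored. The sentence and the comparator should be corrected before analysis, but the point does not threaten the primary result.

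**What to change.** **Main change**

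1. Label the subgroup model as conditional on survival to three months, consent and interview.
2. Compare it only with the same VABS-II ≥70 model refitted in all interviewed survivors. The two sets then differ only by baseline PCPC.
3. Remove the claim that the subgroup allows comparison with the all-patient model.

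This takes a change of wording and one extra model fit on data already held. The downside is that the comparison no longer speaks to the all-patient model.

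**Optional addition**

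As a sensitivity analysis that keeps deaths, refit the all-patient model in children without a PIM-3 high-risk comorbidity, a Box 1 variable from the registry data. The flag must be defined to leave out the cardiac-arrest category: Identification and screening describes arrest before admission as a PIM-3 high-risk category, so otherwise every eligible child would be positive. The downsides are that the flag measures baseline function more coarsely than PCPC, and that it drops out as a predictor in the restricted set.

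**Not as a main repair**

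Imputing baseline PCPC for children who died would rest entirely on survivors, because no death has an observed value, and the assumption could not be tested.

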### External validation of the NEUROPACK prognostic score

As part of the process of ensuring a prediction model is considered clinically useful, it must be validated in an external dataset.^27^ We aim to do this by validating the NEUROPACK prognostic model in the publically accessible dataset for the Therapeutic Hypothermia After Paediatric Cardiac Arrest OHCA and IHCA randomised controlled trials in the National Institute for Health Biolincc repository (Http://biolincc.nhlbi.nih.gov).^2 3^ The sample size of the dataset to be used for external validation should be sufficient to provide reliable and accurate results. To externally validate the model, predictions of risk for each patient in the external validation dataset are made, and performance statistics, such as the C-statistic, are calculated in the same manner as described earlier.

## Patient and public involvement

Given the sensitive and emotive nature of the NEUROPACK study, and the need for active parent and family engagement throughout, a patient advisory group, consisting of parents with experience of critical illness and death in children, and the Clinical Research Network: Children young person’s advisory group (a sub group of the Generation R group aged 9–17 years) have been consulted in designing the protocol, the informational material to support the intervention, and to understand the burden of the intervention from the patient’s perspective. At the end of the study, the patient advisory group will be consulted on findings and contribute to the dissemination plan.

## Ethics and dissemination

PICANet has ethical approval as a research database granted by the East Midlands, Derby Research Ethics Committee (ref 18/EM/0267) and NHS Health Research Authority Confidentiality Advisory Group approval (ref PIAG 4–07/(c)2002) to collect personally identifiable data without consent. The PICANet Clinical Advisory Group has approved pseudonymised sharing of PICANet audit data for the NEUROPACK study and Data Sharing Agreements will be established with the data controllers for the PICANet dataset prior to the release of de-identified PICANet and NET-PACK 3 data. Quality control of NET-PACK 3 customised data collection, data definitions and data collection is performed by the PICANet team.

Regional Ethics Committee (REC) permission has been obtained (Wales Research Ethics Committee 5, 17/WA/0306). This permits the ethical approach and consent of parents/guardians of eligible children who are likely to survive to 3 months following CA to enable telephone VABS-II assessment and identified data-linkage and sharing with PICANet and NET-PACK3 data.

We aim to publish the results in peer-reviewed journals and present at relevant national and international conferences.
